#### Trial measures and data collection

The following measures and data collection methods will be used to assess trial feasibility and acceptability:

**Eligible patients’ consent rate**

We will assess eligible patients’ consent rate at each hospital site. A researcher will record the number of eligible patients who consent to the study. Based on our previous study of a physical activity intervention for people with stoma [47] and people with bowel cancer [50], we estimate a 30% consent rate.

**Acceptability of randomised controlled design**

Eligible patients’ consent rate and the retention rate for the study will be used as proxies for acceptability of a randomised controlled trial design. The retention rate is defined as the number of consenting participants who complete baseline and follow-up measures. Based on our previous study of a physical activity intervention for people with stoma [47], we estimate a 60% retention rate.

**Acceptability and data availability of outcome measures**

The acceptability of measures of outcomes will be explored in the semi-structured interviews conducted with participants at the end of the study (see above). Data availability refers to the amount of data available for analyses. In a future fully powered trial, only complete data (i.e., individually paired baseline and follow-up data for the primary outcomes) will be included in the analyses. In this feasibility study, we will therefore assess the amount of complete data for endpoints and other outcomes (Table 2).

**Table 2 Tab2:** Endpoints and measures

Outcomes	Measures
Diagnosis and classification of PSH	• Clinical examination
Muscle activation	• Electromyography (EMG)
Body composition	
Waist circumference BMI	• Measuring tape • TANITA scales (weight) and stadiometer (height)
Patient reported outcomes	
QoL Body image Physical functioning	• Stoma-QoL and EQ-5D • Body image scale • Patient specific function scale
Physical activity	• Actigraph GT3X+ accelerometer
Psychological determinants of physical activity	• Basic psychological needs in exercise scale • Exercise self-efficacy

***Diagnosis and classification of bulge/PSH***

Documentation of the size of a bulge/PSH and changes over time will be assessed by clinical examination. There is no gold standard examination to assess, diagnose and classify PSH [3]. CT is highly accurate at identifying PSH but is difficult to justify because of cost, and there is risk of radiation exposure. A radiologist and medical physicist in one of the research sites had ethical concerns about increased radiation exposure, particularly in young adult participants with inflammatory bowel disease (IBD). They also were not confident that there was capacity to meet the study’s baseline and follow-up timepoints due to pressure on this resource for clinical purposes. Hence, it was decided to use clinical examination to diagnose and classify bulge/PSH. Clinical examination has sensitivity rates between 66 and 94%, and specificity rates are reported to be as high as 100% [3]. The grade of PSH will be recorded using a classification system recommended by the European Hernia Society [3, 45]. Each participant will have a clinical examination by a member of their clinical team (e.g., surgeon or nurse).

As illustrated in Fig. 1, we hypothesise that the PA intervention will lead to improved muscle activation, prevent muscle atrophy in the stoma area, and improve muscle density via activation and control. We also hypothesise that patient-level risk factors such as BMI and waist circumference will be reduced by the PA intervention.

***Muscle activation***

Any changes to muscle activation will be assessed using electromyography (EMG) to record the electrical activity of the abdominal muscles [51]. The EMG will record the electrical activation of the cells to demonstrate the level of contraction achieved.

***Body composition***

An abdominal CT scan would allow assessment of the physiological changes and body composition because it would enable calculation of abdominal muscle density and abdominal muscle/adipose tissue ratio by analysing the L3 lumbar muscle segments of each participant. Abdominal circumference measurements and assessment of abdominal adiposity can similarly be calculated. However, as described in the previous section, a decision to not use a CT scan in this study was made. The following non-invasive methods for measuring body composition will therefore be adopted instead:

Waist circumference will be measured by a researcher who will receive written and pictorial instructions on proper performance of the measurement [52]. All measurements will be performed using the MyoTape (AccuFitness, LLC) on bare skin or over thin garments. BMI is an easily calculated assessment of body weight adjusted for height (weight in kilograms/height in metres). Body weight (kg) will be measured by a researcher using TANITA scales. Patients will be asked to remove any outer garments, take off shoes and empty pockets. Stadiometers will be used to measure height (cm). Patients will be instructed to remove their shoes, stand with feet flat on the floor, feet together and heels against the wall, and with shoulder blades and buttocks also touching the wall, arms hanging loosely by their side, and facing straight ahead. They will be instructed to breathe in deeply and stretch to their fullest height when the measurement is taken. BMI will be calculated from these measurements using the standard formula of weight (kg)/height (m)^2^. BMI scores can then be translated into the following categories underweight, normal weight, overweight or obese.

***Patient reported outcomes: quality of life, body image and physical functioning***

In a future full-scale trial, we intend for QoL to be the primary outcome; this variable provides us with the patient perspective of the intervention’s direct clinical benefit and is an outcome that is considered important to patients [53]. To our knowledge, there are no bespoke instruments for assessing PSH-related QoL or for body image in this group. There are, however, generic QoL and body image instruments and several stoma-specific QoL tools [54] that we will use. PSH-specific questions will be incorporated. We will use the following instruments that will be completed by participants at baseline and follow-up. Each participant will meet with a researcher face to face to complete questionnaires hosted by Bristol On-line Survey, which is an online service that allows researchers to develop, deploy and analyse an online survey. Which instruments we use in the planned full trial will be decided by the independent Study Steering Committee (see Main outcome of feasibility section) who will draw on completion rates for each measure alongside qualitative data from participant interviews about the relevance and acceptability of each measure to make an informed decision.

The generic QoL instrument that we will use is the European Quality of Life-5 Dimensions (EQ-5D-5L), which is common measure of health-related quality of life [55]. It is divided into two sections: the EQ-5D index and the EQ thermometer. The EQ-5D index assesses health across five domains: mobility, self-care, usual activities, pain/discomfort and anxiety/depression. The EQ thermometer is a single 20-cm vertical visual analogue scales with a range of 0 to 100, where 0 is the worst and 100 is the best imaginable health and is completed by the user for their current health. Descriptive data from the five dimensions of the EQ-5D part 1 can be used to generate a health-related quality-of-life profile for the subject, created from the 1–5 scale for each question. This can be further divided into those reporting ‘problems’ or ‘no problems’, combining some of the subscales. Part 2 is scored from 0 (worst health state imaginable) to 100 (best health state imaginable). The score from part 2 can be used to track changes in health, on an individual or group level, over time. Simulation-based estimates (mean score) of the minimal important difference (MID) of the EQ-5D-5L index score in 6 countries (including England) were generally between 0.037 and 0.069, which are similar to the MID estimates of other preference-based QoL measures [56]. The MID (mean and standard deviation) for England was 0.037 ± 0.008).

Stoma-related QoL will be measured using the Stoma-QoL [57], which was deemed acceptable for use by participants in our previous study [37]. It is a 21-item questionnaire; 19 items covering the 5 domains of work/social functioning, sexual/body image, stoma function, financial concerns, and skin irritation are scored using a 5-point Likert-type frequency scale, and 2 items measure overall life satisfaction and are scored from 0 to 100, with 0 being the worst possible score and 100 being the best score. To our knowledge, no recommended MID estimates have been published for this instrument.

The body image scale [58] will be used for assessing body image. It was chosen because it has been validated in ostomy patients [59]. It is a 10-item questionnaire with items scored using a 4-point rating scale that was developed to assess the affective (e.g., feeling self-conscious), behavioural (e.g., difficulty in looking at the naked body) and cognitive (e.g., satisfaction with appearance) aspects of body image in cancer patients.

The Patient-Specific Functional Scale (PSFS) focuses on the patient’s opinion of their function in order to provide clinicians with a reliable and valid self-reported outcome measure [60]. The patient lists up to five activities that are limited by their condition (in this study, bulge/PSH) for which they are seeking treatment (in this study exercise programme). For each activity, patients use a continuous rating scale (0 to 10) with a lower score indicating that they are unable to perform the activity, to indicate the extent to which they are able to carry out the activity. The total score is the sum of the activity scores divided by the number of activities listed. It takes an average of 4 min to complete. It is used in clinical practice and research to assess if there is a meaningful change in functional status that has occurred over time. The MID has been evaluated for certain conditions and is between 2 and 3 [60].

***Physical activity***

The amount of physical activity will be objectively measured using the Actigraph GT3X+ accelerometer (Actigraph LLC, Pensacola, FL, USA) [61]. Accelerometers record movement in such a way that it can be translated into a number of different outputs, for example total step count, bouts of physical activity at specified intensities or energy expenditure. This measure will be used to examine how physical activity levels change over the course of the study. It will be worn around the wrist and measures activity counts, steps, inclinometers, and light and moderate-to-very-vigorous physical activities. Participants will be given an accelerometer that will be worn during waking hours for 7 consecutive days for 1 week at baseline and follow-up. At the end of the 7-day period, participants will return the device to the research team.

Accelerometer devices will be initialised by a researcher as follows: (1) Device recording of physical activity will be set for 7 days, with the intention to gain a minimum of 4 valid days of data for each participant; (2) the date and time when the participant is scheduled to wear the device will be set. The sample rate will be set to 30 Hz; (3) the unique participant ID will be added to the specific device.

Once the device is returned by a participant, the Actigraph software will be used to download data, as follows: (1) The unit of measurement will be set at 10-s epochs; (2) the ‘# of axis’ setting will be set to 3, and ‘steps’, ‘lux’, ‘inclinometer’ and ‘low frequency extension’ will all be selected. The Actigraph software wear-time validation will be set to meet the following criteria: (1) minimum number of valid days required = 4; (2) non-wear time will be set at > 60 min of consecutive zeros; (3) minimum number of wear hours per day required will be set at > 10 h (600 min). Commonly reported cut-points for adults will be used to differentiate physical activity intensity using Freedson et al. [61].

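### Wrist-worn accelerometer data are graded with general adult count cut-points that the protocol does not show to be valid for that placement and those settings

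*Protocol article*

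**What the plan says.** All of the relevant text is in the Physical activity subsection of the Protocol article, under Trial measures and data collection.

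- **Device and purpose.** Activity is to be "objectively measured using the Actigraph GT3X+ accelerometer", and "This measure will be used to examine how physical activity levels change over the course of the study".
- **Placement and outputs.** "It will be worn around the wrist and measures activity counts, steps, inclinometers, and light and moderate-to-very-vigorous physical activities".
- **Recording.** It is worn during waking hours for 7 days at baseline and again at follow-up, sampled at 30 Hz.
- **Download.** "The unit of measurement will be set at 10-s epochs"; the number-of-axes "setting will be set to 3"; and "low frequency extension" is among the options selected.
- **Wear-time rule.** At least 4 valid days are required, each with more than 10 hours of wear. Non-wear is more than 60 minutes of consecutive zeros.
- **Grading.** "Commonly reported cut-points for adults will be used to differentiate physical activity intensity", with a single citation (reference 61), which is also the citation given for the device.

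No count thresholds are printed. The text does not say at which body site, on which axis, in which epoch or with which filter the cut-points were derived, or that they have been adapted to wrist wear.

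**The concern.** A count cut-point is a calibration. It converts device counts into an intensity category, and the counts depend on where the device sits and on how the signal is filtered and summed. Thresholds derived at one site with one set of processing choices do not carry over to another without evidence. Here placement, axes, epoch and filter are all fixed, and a general adult set is then applied with no stated link to any of them.

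The accelerometer is the only measure listed for physical activity in Table 2; the participants' diaries are self-report. Low physical activity is one of the risk factors that the Background and the theory section expect the intervention to change. The Data analysis section has all outcome measures summarised by arm and time point with 95% confidence intervals, so misgraded minutes would be reported with apparent precision, and the method could carry over into a full trial.

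**Working it through.** **1. Setting the statements side by side**

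| Element | Fixed in the protocol | Shown to match the cut-points? |
|---|---|---|
| Wear site | wrist | no |
| Axes | 3 | no |
| Epoch | 10 s | no; no scaling of thresholds stated |
| Filter | low frequency extension selected | no |
| Cut-points | general adult set, reference 61 | no values or calibration conditions given |

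The epoch alone is not an error, because per-minute thresholds can be scaled to 10 seconds. The gap is that no scaling is stated.

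**2. Direction**

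Let *k* be the ratio of counts under the protocol's set-up to counts at the calibration site. Minutes above a fixed threshold are unchanged at *k* = 1, overstated for *k* > 1 and understated for *k* < 1. The documents give no value of *k*, and the protocol states no expected minutes, so there is no figure of its own to reproduce.

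**3. Does the error cancel in the change?**

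This is an illustration only, and every input is an assumption: 840 minutes of wear a day (14 h), log-normal counts per minute with log SD *s* of 1.2 or 1.5, 3% of minutes truly above the threshold, and one constant *k*.

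- True minutes: 840 × 0.03 = 25.2.
- The standard normal upper 3% point is *z* = 1.881.
- Graded minutes = 840 × P(Z > 1.881 − ln *k* / *s*).
- A true 30% rise takes 3% to 3.9%, with upper point 1.762. True minutes become 840 × 0.039 = 32.8, a gain of 7.6.

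Worked case, *k* = 2 and *s* = 1.5: ln 2 / 1.5 = 0.462. Before the rise, 840 × P(Z > 1.419) = 65.5. After it, 840 × P(Z > 1.300) = 81.3. The gain is 15.8 minutes, or 24%.

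| *k* | Graded min/day before, *s* = 1.5 / 1.2 | Apparent gain, min/day | Apparent gain, % |
|---|---|---|---|
| 0.5 | 8 / 6 | 2.9 / 2.2 | 37 / 38 |
| 1 | 25 / 25 | 7.6 / 7.6 | 30 / 30 |
| 2 | 66 / 81 | 15.8 / 18.3 | 24 / 23 |
| 3 | 105 / 140 | 21.9 / 26.3 | 21 / 19 |
| 4 | 142 / 197 | 26.5 / 31.8 | 19 / 16 |

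The same true change appears as a different change, in minutes and in per cent, according to *k*. For *k* > 1 the absolute gain is inflated and the relative gain shrunk; for *k* < 1 both reverse. The model shows distortion of both level and change. It says nothing about which *k* applies.

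**4. What is not touched**

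The Acceptability and data availability section asks how much complete paired data there is. For this endpoint that depends on valid days and wear time, not on intensity cut-points. The sample size of 20 does not depend on them either.

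**The case against.** The strongest reply is that nothing in the subsection contradicts itself. The cited source is not available, so its calibration conditions are unknown here. The axis and filter entries are download settings; the text does not say which axis or composite is compared with the thresholds, and such scoring detail is often left to a fuller document. The study is a descriptive one with 20 participants, its feasibility question for this endpoint is completeness, and quality of life is the intended primary outcome of the full trial. Step and count outputs need no intensity cut-point. Identical settings apply in both arms and at both visits, and the data can be reprocessed.

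Much of this stands, and it limits the point. A reader might infer that the cut-points are a hip-worn, single-axis set, and that the minutes will therefore be badly overstated. The documents support neither: they give no calibration site and no count ratio. They also give no ground for saying that the inclinometer output is invalid at the wrist, or that the Steering Committee would choose an activity measure from its baseline level and spread. The stated basis for choosing instruments, in the patient-reported outcomes section, is completion rates and interview findings.

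Two parts of the reply do not hold. Identical settings do not guarantee that the error cancels, because thresholding is non-linear. And this is not merely detail left out: the article itself fixes the placement, the processing and the cut-point source, and the objection is to that stated combination.

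**Conclusion.** The point holds in a limited form. As written, the plan grades wrist-worn, three-axis data, in 10-second epochs with the low frequency extension, using a general adult cut-point set with no indication that the set is valid for that arrangement. The light and moderate-to-vigorous minutes by arm and time point could be misgraded in either direction, and so could their change over the study.

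This rests on the general property that count cut-points are specific to site, axis, epoch and filter, and on the absence of any stated match. The size is unknown; the tabulated figures only illustrate the mechanism and are not estimates for this trial. What is affected is the reported intensity minutes and the stated aim of examining change with the only objective activity measure. Data-availability rates, the sample size and the quality-of-life outcomes are not affected.

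**What to change.** Keep wrist wear. Replace the cut-point sentence with one that:

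1. names intensity thresholds validated for adult wrist wear;
2. states the axis or composite, the epoch and the filter they were derived with, and processes the data to match, including any scaling to 10-second epochs;
3. makes a cut-point-free summary the main activity measure, such as mean daily acceleration from the 30 Hz recording or total counts, with intensity minutes reported as secondary.

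The cost is one paragraph of wording and a changed processing step on recordings the study already plans to collect. Nothing changes for participants. The small downside is less direct comparability with studies that used the general adult cut-points.

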***Psychological determinants of physical activity***

The Basic Psychological Needs in Exercise Scale assesses [62] determinants of physical activity from the perspective of the self-determination theory, which is the theory underpinning the intervention [41]. This is an 11-item self-report questionnaire. Participants rate each item on a 5-point scale from 1 (I don’t agree at all) to 5 (I completely agree). Items assess participants’ need fulfilment for autonomy, competence and relatedness. In line with the self-determination theory, the satisfaction of these needs results in higher levels of behavioural self-determination that in turn, is reflected by higher levels of, for example, intrinsic motivation (e.g., finding exercise enjoyable) and identified regulation (e.g., considering exercise outcomes to be personally important).

#### Participant timeline

Figure 2 illustrates the process of enrolling participants in the study and timing of intervention and measurements.

**Fig. 2 Fig2:**
[figure not shown]
Participant flowchart

#### Sample size and randomisation

The current study will confirm the feasibility of recruiting and retaining patients with stoma based on the rates obtained from our previous physical activity trial in this sample as outlined above. In a future full-scale trial, we intend for QoL to be our primary outcome; based upon the review above [30], we anticipate a large effect size. Therefore, in line with Whitehead et al., a sample size of 20 is appropriate [63].

Participants will be randomly allocated to intervention and control groups by a researcher using MinimPy (http://minimpy.sourceforge.net/introduction.html), which is a free randomisation software package to manage the process of minimizing the difference among trial groups with respect to preselected categorical factors, i.e., age and gender.

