## Methods

### Project design

This is a feasibility study of a randomised controlled trial with 2 months follow-up, in 2 sites, with 20 participants, using mixed methods. Stage 1 involves intervention development and in stage 2, intervention and trial parameters will be assessed.

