**Hospital**

A list of potentially eligible patients will be put together by the hospital clinical team who will send a letter of invitation to those that are eligible. Patients who are interested in the study will get in touch with the research team by post, telephone, or email expressing an interest in the study. A researcher will contact the potential participant by email or telephone to explain the study in more detail and confirm eligibility. Written information, in the form of a participant information sheet (PIS), will be sent to potential participants. The PIS will describe the nature of the study, what it will involve, and the known risks of taking part. Written informed consent will be obtained at a face-to-face meeting that will be arranged to coincide with the administration of baseline measures.

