#### Data analysis

Intervention parameters (fidelity, adherence, acceptability and safety) and trial parameters (eligible patients’ consent, retention and data availability rates) will be reported overall and by site. Reasons for non-fidelity, non-adherence, non-consent, non-randomisation, and non-availability of data will be summarised. Follow-up rates will be reported overall, by site and by arm to demonstrate the acceptability of the schedule for both arms. The analysis will focus on confidence interval estimation rather than formal hypothesis testing. All outcome measures will be summarised by arm, at each time point together with 95% confidence intervals. Levels of missing data for all outcomes will be summarised overall and by arm. AEs will be monitored and rates compared descriptively between study groups. Qualitative thematic analyses of audio-recorded interviews and focus groups will be conducted using the Framework approach [64]. These data will inform the decision to proceed to a Phase III trial (Table 1).

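### Minimisation balances age and gender but not site, so in this two-site trial the arms can by chance be unevenly spread across the hospitals

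*Protocol article*

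**What the plan says.** The protocol article, under Project design, describes a study "in 2 sites, with 20 participants, using mixed methods". Under Sample size and randomisation, allocation is by minimisation: "Participants will be randomly allocated to intervention and control groups by a researcher using MinimPy", with the software "minimizing the difference among trial groups with respect to preselected categorical factors, i.e., age and gender". The wording closes the list at those two factors, and site is not one of them.

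Site nevertheless appears in the planned reporting. Under Data analysis, intervention and trial parameters are given overall and by site, and "Follow-up rates will be reported overall, by site and by arm to demonstrate the acceptability of the schedule for both arms". All outcome measures are summarised by arm at each time point. The same section says: "The analysis will focus on confidence interval estimation rather than formal hypothesis testing". Under Diagnosis and classification of bulge/PSH, each participant is examined and graded by a member of their own clinical team, who may be a surgeon or a nurse.

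The article does not give the split of participants between hospitals, the age categories, the allocation ratio, or whether the minimisation has a random element.

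**The concern.** Minimisation controls balance only on the factors it is given. With about 20 people and site left out, nothing keeps the two arms evenly represented at each hospital. If one arm is drawn mainly from one hospital, a difference between hospitals in retention, or in how examiners grade a hernia, shows up as a difference between arms. The quantity most exposed is follow-up by arm, which the article names as its evidence that the schedule is acceptable in both arms. The by-arm summaries of hernia grade are exposed too, because the examiners differ between hospitals.

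**Working it through.** **No figure in the plan to reproduce.** The only number in the randomisation section is the sample size of 20, which this point does not dispute. The check is a simulation of the allocation rule.

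**Inputs from the article:** 20 participants, 2 sites, minimisation on age and gender.

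**Assumptions, because the article does not give them:** 1:1 allocation; sites split 10/10 (alternative 14/6); age in two categories (alternative three); two gender categories; all categories equally common; participants from the two sites arriving in random order; favoured arm chosen with probability p = 1.0 (deterministic), 0.8 or 0.7.

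**Rule:** for each new participant, add up over the factors the existing difference between arms at that participant's level. If the sum is zero, allocate at random; otherwise choose the arm that reduces the sum, with probability p. There were at least 4,000 simulated trials per setting, repeated independently with results agreeing to within about one percentage point.

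**Result 1: balance within site.** The chance that the arms differ by 4 or more at one or both sites (7:3 or worse with a 10/10 split), with binary factors:

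| p | Age and gender | Age, gender and site |
|---|---|---|
| 1.0 | about 20% | 0% |
| 0.8 | about 27% | about 6% |
| 0.7 | about 34% | about 17% |

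Across the alternative site split and three age categories, the ranges without site are 17–22%, 24–29% and 30–34% for the three values of p. With site they are 0%, 5–6% and 15–18%. A difference of 6 or more occurs in 1.5–7% of trials without site. A site falling wholly into one arm, with a 10/10 split, occurs in about 0.1% or fewer.

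**Result 2: what such a split does to follow-up by arm.** Take 7:3 at one site and 3:7 at the other. One arm has 70% of its members from the first site and the other has 30%. If retention differs between sites by d points, the arm difference shifts by (0.7 − 0.3) × d:

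- d = 10 gives 4 points
- d = 20 gives 8 points
- d = 30 gives 12 points

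The value of d is an assumption. For scale, at the article's expected retention of 60% and 10 per arm, the standard error of the arm difference is √(2 × 0.6 × 0.4 / 10) = 0.219, or about 22 points.

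**Result 3: predictability.** The share of allocations guessed correctly (10/10 split, binary factors; chance is 50%):

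| Guesser knows | p | Without site | With site |
|---|---|---|---|
| All earlier allocations, both sites | 1.0 | about 85% | about 88% |
| All earlier allocations, both sites | 0.8 | about 72% | about 74% |
| Own site only | 1.0 | about 59% | about 74% |
| Own site only | 0.8 | about 58% | about 65% |

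Adding site repairs the balance and makes the next allocation somewhat easier to guess, most of all for a local researcher when the rule is deterministic.

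**The case against.** The strongest reply is that little here depends on balance of arm by site. The analysis is descriptive. Consent rate is settled before allocation. Fidelity, adherence, intervention acceptability and safety describe people who receive the intervention, not a contrast between arms. Reporting by site will also let a reader see site differences. A shift of 8 points is well inside a standard error of about 22 points. All of this stands, and it is why the point is modest. It does not remove the point, because the imbalance comes from a stated rule and can be avoided at almost no cost.

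A second reply is that leaving site out makes allocation harder to guess for someone at one hospital. That is true, and the fix has to answer it.

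Stronger readings are tempting, and the article does not support them:

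- **That arm and site are confounded.** A 7:3 split is chance imbalance; near-complete separation is very rare.
- **That the next allocation is largely predictable.** The 85% figure needs a deterministic rule, which the article does not state, and knowledge of every earlier allocation at both sites. A researcher who knows only their own site is right about 58–59% of the time under the present factors.
- **That the allocating researcher also recruits and measures.** The same general label is used elsewhere, for example "A researcher will contact the potential participant by email or telephone to explain the study in more detail and confirm eligibility" and "Each participant will meet with a researcher face to face to complete questionnaires". But the article also refers to researchers in each site and to research assistants, and never says that one person does all of this. Who operates the software, how allocation is concealed and which random element is set are details a condensed article may leave to the full protocol.
- **That the full trial would inherit this procedure.** No allocation method for the full trial is given.

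**Conclusion.** The point holds in a limited form. Site is missing from a closed list of minimisation factors in a two-site trial that reads follow-up by site and by arm. Under the assumed 10/10 split and binary factors, the arms divide 7:3 or worse at one or both sites in about 20% of trials (deterministic) to 27% (p = 0.8); the other settings examined span 17–34%. By-arm follow-up and outcome summaries can therefore carry chance differences between sites, by an amount smaller than the sampling error of a 20-person study. The percentages depend on the assumed site split, factor levels, prevalences and random element, but the direction and rough size were the same in every setting tried. It is worth changing, but it does not threaten the study's purpose.

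**What to change.** Add site as a third minimisation factor and state the random element, for example a probability of 0.8 for the favoured arm. With these settings the chance of a 7:3 or worse split at a site falls to about 6%.

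State the cost alongside it: the next allocation becomes somewhat more predictable, about 72% to 74% with the full history and about 58% to 65% for a researcher who knows only their own site. The random element matters here, since under a deterministic rule the local figure would rise from about 59% to 74%. To offset this, have existing staff at the other site run the software for each participant, so that the recruiting site does not hold the combined history. If the full protocol already sets a random element or a separate operator, only the site factor needs adding.

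The practical cost is one added factor, one software setting and a message between sites for each participant. No extra staff or participants are needed.
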